### Operation

All patients will receive standard monitoring with ECG, pulse oximetry, a radial arterial line with cardiac output monitor attached to a Vigileo monitor (Flotrac MHD8R, Edwards Lifesciences, Dominican Rep). Central line and a pulmonary arterial catheter (either 7.5F CCO: 139HF75P or 7F TD: 131 F7, Edwards Lifesciences, Irvine, USA) will be inserted after intravenous induction of general anaesthesia. The techniques of anaesthesia and cardio-pulmonary bypass (CPB) will be standardized. After premedication with benzodiazepines, anaesthesia will be induced with iv propofol (1-2 mg/kg) and fentanyl (10-20 μg/kg); muscle relaxation will be achieved with rocuronium (1 mg/kg), vecuronium (0.2 mg/kg) or pancuronium bromide (0.1 - 0.2 mg/kg). The airway will be intubated and mechanically ventilated with oxygen, air and isoflurane 1-2%. Propofol and remifentanil infusion may be used in addition to isoflurane for maintenance of anaesthesia.

Intravenous fluids (Hartmann' s solution or gelofusin), vasopressors (metaraminol or phenylephrine) and inotropes (enoximone or milirone, dopamine, noradrenaline and adrenaline etc.) will be titrated according to patients' haemodynamic status. Prophylactic antibiotics (cefuroxime and teicloplanin) and antifibrinolytic agents such as tranexamic acid (2 g) will be administered prior to sternotomy.

Operative monitoring will be identical in all patients. The extracorporeal circuit will comprise a Stockert roller pump (Shiley Inc, Irvine, CA), a Shiley S100 membrane oxygenator, and polyvinylchloride tubes. Patients will be given heparin just before the institution of CPB with 300 IU/kg, with additional dosing as necessary to maintain the activated clotting time greater than 480 seconds. Non-pulsatile extracorporeal circulation will be initiated at flows of 2.4 to 2.6 L m^-2 ^min^-1^. Moderate systemic hypothermia (32°C nasopharyngeal) will be uniformly used. Cardiac arrest will be achieved by infusion of 1 L of cold blood cardioplegic solution and topical slush.

All distal anastomoses will be performed during a single period of cross clamping, and the proximal anastomoses to the aorta will be completed during the re-warming period. Extracorporeal circulation will be terminated at a nasopharyngeal temperature of 37°C. Heparin will be neutralized after the end of CPB with protamine sulphate (1 mg/100 IU heparin).

Before weaning from the cardio-pulmonary bypass circuit, temporary unipolar epicardial pacing wires will be sutured to the roof of the right atrium, the right ventricular outflow tract and the postero-lateral free wall of the left ventricle (first obtuse marginal territory) avoiding scar tissue. There will be a total of 6 wires, 3 active and 3 indifferent wires. The wires will be attached via extension cables to a temporary external triple chamber pacemaker (Osypka PACE 300, Germany).

Pacing will be commenced prior to separation from the bypass circuit according to each patient's randomisation. Subjects in the BiV group received DDD-BiV pacing, base rate 90 bpm, AV interal 120 msec, max tracking rate 110 bpm, VV interval -5 msec (-ve indicating LV pre-activation). The standard pacing group received AAI pacing at base rate 90 bpm unless ventricular pacing will be indicated. In this situation DDD-RV pacing will be programmed, base rate 90 bpm, AV interval 150 msec and max tracking rate 110 bpm. RV pacing will be kept to a minimum.

Inotropes including, enoximone or milrinone in combination with noradrenaline will be administered according to haemodynamic requirements. The target range for haemodynamic parameters after surgery:

• Mean arterial pressure 60-70 mm Hg

• Pulmonary capillary wedge pressure < 18 mm Hg

• Cardiac index 2.0-2.5 L/min/m^2^

### Haemodynamic studies

Haemodynamic studies will be performed after admission to the CITU after surgery (time = 0). The first study will be performed using a pulmonary arterial (PA) catheter, once the subject is euvolaemic and has a stable inotropic requirement. Cardiac output/index, pulmonary artery pressures, pulmonary capillary wedge pressure, central venous pressure, mean arterial pressure (MAP) and LV stroke work index will be recorded.

For thermodilution measurements, 3-5 sets of cardiac output measurements will be obtained to ensure consistent results. Measurements will be taken in the following pacing modes: atrial inhibited (AAI), right ventricle only (VVI), dual chamber (DDD-RV) and (DDD-LV) and BiV pacing. A minimum of 5 minutes will be allowed between changing the pacing mode and obtaining haemodynamic data. A pacing mode will be discontinued if it causes > 10 mm Hg drop in MAP. The base rate of pacing will be set at 10 beats above intrinsic rhythm up to a maximum heart rate of 110 bpm. The pacing modes will be selected at random. The studies will be repeated at 6 hours, 18 hours and 24 hours. After the 24 hour measurements the PA catheter will be removed. Cardiac output data will be also obtained from the radial pulse contour analysis (FLOTRAC) monitor at the same time points as the PA catheter, except for subjects with an intra-aortic balloon pump.

Optimisation of the atrio-ventricular (AV) and interventricular (VV) delays will be performed at 18 hours. A range of AV delays from 80-180 msec in 20 msec intervals and then VV delays from -40 to 40 msec (-ve indicating LV pre-activation) in 20 msec intervals will be performed. The optimal AV and VV delays will be programmed for patients assigned to BiV pacing.

### Endpoints

The primary endpoint of the trial is the duration of level 3 care [22] required after cardiac surgery. Level 3 care is defined as the duration of invasive mechanical ventilation or multiple organ support or multiple inotropes/single inotrope and intra-aortic balloon pump. The majority of patients would reach the primary endpoint after extubation and then once weaned down to a single inotrope. In the cases where inotropes are restarted, the endpoint is taken to be the final transition from level 3 to level 2 care before discharge from the intensive care unit.

Secondary endpoints are:

• Cardiac index at 18 hours (AAI v BiV).

• Duration and total dose of inotropes/intra aortic balloon counter-pulsation.

• Renal function and requirement for haemofiltration.

• Arrhythmia after surgery until hospital discharge.

• Change in brain naturetic peptide, troponin T and neutrophil gelatinase associated lipocalin.

• Myocardial infarction, re-intubation or re-sternotomy.

• 30 day all cause mortality.

Subjects will complete the trial 30 days after the operation.

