## Background

The prevalence of heart failure is increasing throughout the industrialised world. Approximately 2-3% of the general population are diagnosed with heart failure [1] and the primary aetiology is coronary artery disease. A retrospective analysis of heart failure trials has identified at least 62% of subjects have coronary disease [2]. The total financial cost to the National Health Service is approximately £ 563 million per annum in 2006-7[3].

Modern medical therapy has substantial reduced both morbidity and mortality after a myocardial infarction. ACE inhibitors [4,5], beta blockers [6-8] and aldosterone antagonists [9,10] modulate the renin-angiotensin-aldosterone axis and neurohormonal cascade which reduces major adverse events. These medications arrest the cascade of progressive ventricular remodelling and dilatation observed in heart failure. Further ventricular remodelling can be achieved with biventricular (BiV) pacing through the reversal of electro-mechanical dyssynchrony. The reduction in ventricular volumes correlates to a reduction in heart failure events, arrhythmias and death [11,12].

Heart failure patients with stable angina and a significant burden of coronary artery disease may benefit from surgical revascularisation. However, the risk of surgery is increased and mortality rates range from 5-30% [13]. There is limited randomised control data on surgical revascularisation in subjects with severe left ventricular (LV) systolic dysfunction- ejection fraction ≤ 35%. The landmark trials of surgical revascularisation in the 1970 excluded subjects with significant LV dysfunction [14,15].

The Coronary-Artery Bypass Surgery in Patients with LV Dysfunction (STICH) trial was specifically designed to address this issue and compared optimal medical therapy to surgical revascularisation, in subjects with severe LV systolic impairment [16]. The primary endpoint of all cause mortality was not significant between the 2 groups at 56 months follow-up (41% medical v 36% surgical; p = 0.12). However, the secondary endpoint of death or cardiovascular hospitalisation was less likely in the surgical group (68% v 58%; p < 0.001).

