Data obtained for the primary endpoint and haemodynamic studies will be analysed for normality using the Kolmogorov-Smirnov test. Normally distributed variables will be analysed using unpaired or paired Student's T tests respectively. Non-parametric data will be analysed using the Mann-Whitney U or Kruskal-Wallis test. If continuous variables are not matched between intervention and control groups at baseline, inter-group comparisons will be made using an analysis of covariance with adjustments made for baseline differences. Changes in proportions for categorical data will be analysed with the Chi-square test or Fisher's exact test.

Analysis will be intention-to-treat and a p-value of < 0.05 will be considered statistically significant.

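### The primary duration ends only by recovery, so the stated tests must either exclude a patient who dies on level 3 care or use a value cut short by death

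*Protocol article*

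**What the plan says.** The Endpoints section states: "The primary endpoint of the trial is the duration of level 3 care [22] required after cardiac surgery". Level 3 care is defined there by invasive ventilation, multiple organ support, or more than one inotrope (or one with a balloon pump). Two sentences say how the duration ends. For most patients: "The majority of patients would reach the primary endpoint after extubation and then once weaned down to a single inotrope". After an inotrope restart, "the endpoint is taken to be the final transition from level 3 to level 2 care before discharge from the intensive care unit". Both are recovery events.

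Death appears in that section only as a separate secondary endpoint, "30 day all cause mortality". Follow-up is fixed by "Subjects will complete the trial 30 days after the operation".

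Under Statistical Analysis, the primary endpoint is first tested for normality. Then: "Normally distributed variables will be analysed using unpaired or paired Student's T tests respectively"; otherwise Mann-Whitney U is used for two groups. The section closes: "Analysis will be intention-to-treat and a p-value of < 0.05 will be considered statistically significant". It names no censoring, competing-risk or worst-rank rule. The Background says of this population that "the risk of surgery is increased and mortality rates range from 5-30" per cent.

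**The concern.** A t-test or Mann-Whitney test needs one number per patient, and intention-to-treat needs that number for every randomised patient. A patient who dies on level 3 care is never weaned and never steps down, so the recovery events that close the duration do not occur. Two routes remain within the stated plan:

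- Exclude the patient. This breaks intention-to-treat and removes patients because of a post-randomisation event that treatment may affect.
- Count time on level 3 up to death. The value is then truncated by death. If death is early it is a short duration, and the protocol's Hypothesis and Summary treat a shorter duration as benefit.

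So the endpoint does not order patients by how well they did. If early deaths differ between arms, the arm with more of them can gain on the primary endpoint. The protocol gives a reason to expect a difference: its Table 3 lists reduced mortality with biventricular pacing in the same study that supplies the sample-size inputs. If pacing does prevent early deaths, time-to-death scoring would place the short values in the control arm and hide part of the benefit.

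**Working it through.** **Inputs from the protocol.** Control mean 3.9 days and SD 0.6 (intensive care stay, used as a stand-in for level 3 duration); target reduction 15%; 80% power; two-sided 5%; total 34; mortality 5-30%. Equal allocation is assumed; it is implied by 16.5 per group becoming 34 in total.

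**1. The plan's own figure.** Target effect: 0.15 × 3.9 = 0.585 days. Per arm: 2 × 7.85 × 0.6² / 0.585² = 5.652 / 0.342 = 16.5, so 17 per arm and 34 in total. The stated figure reproduces. It makes no allowance for deaths.

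**2. Deaths to expect.** 34 × 0.05 = 1.7 and 34 × 0.30 = 10.2. At 5%, the chance of at least one death among 34 is 1 − 0.95^34 = 83%. These count all deaths, so they are upper figures for deaths on level 3.

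**3. Effect of one death on an arm mean.** The shift is (death time − 3.9) / 17. The death times are assumptions; the protocol gives none.

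| Assumed death on level 3 | Shift in arm mean | Share of 0.585 days |
|---|---|---|
| Day 0.5 | (0.5 − 3.9)/17 = −0.20 d | −34% |
| Day 1 | (1.0 − 3.9)/17 = −0.17 d | −29% |
| Day 10 | (10 − 3.9)/17 = +0.36 d | +61% |
| Day 20 | (20 − 3.9)/17 = +0.95 d | +162% |

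The sign depends on when the patient dies.

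**4. False conclusions if mortality differs.** Simulation: 17 per arm, normal durations with mean 3.9 and SD 0.6 in both arms, no true effect, assumed mortality 5% v 20%, deaths scored at an assumed time of 0.25 to 1.5 days. The test wrongly favoured the higher-mortality arm in about 19% of trials by t-test and about 11% by Mann-Whitney (nominal 2.5%). With deaths ranked worst, Mann-Whitney did so in under 1%. Excluding deaths gave no bias here, but only because the simulation made death independent of duration.

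**5. Power with the planned 0.585-day effect, 17 per arm, equal mortality on level 3** (simulation error about 1 percentage point).

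| Scoring and test | No deaths | 10% |
|---|---|---|
| Early deaths scored short, t-test | 79% | 35% |
| Early deaths scored short, Mann-Whitney | 76% | 57% |
| Deaths excluded, t-test | 79% | 72% |
| Deaths ranked worst, Mann-Whitney | 76% | 55% |

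At 5% mortality, worst rank gives about 66%, and Mann-Whitney with early deaths scored short also gives about 66%. So worst rank costs little power beyond what Mann-Whitney already loses with truncated values. It does cost power against excluding deaths, which intention-to-treat does not allow.

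**The case against.** The strongest reply is that this is silence in a condensed article. Scoring of deaths is often left to the full protocol or the SAP, and neither is shown. The quoted step-down rule covers only restarted inotropes, and the basic definition is a duration of care, so a patient who dies on level 3 does have a duration, up to death. Mortality is reported separately, so an imbalance would be seen.

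Part of this stands. The restart sentence is not the whole endpoint definition, and a reader should not infer from it alone that deaths have no value. But the sentence before it also ends the duration by recovery. If duration up to death is the intended reading, that is the truncated value at issue. The article itself fixes the endpoint, the tests and the analysis set, and it is this combination that fails for deaths on level 3. A separate mortality endpoint does not correct the primary comparison.

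The points about size also stand. A reader might infer that deaths always count as short, favourable stays; a late death lengthens the duration. A reader might take 1.7 to 10.2 as deaths on level 3; some deaths will occur after step-down, and the trial excludes emergency revascularisation and dialysis-dependent patients. A single day-1 death does not reverse a 0.585-day effect: with no true effect it raises false favouring of that arm from 2.5% to about 4.6% by t-test or 4.2% by Mann-Whitney. With one 20-day value among 17, the normality test would reject (100% of 1,000 simulations), so the plan would move to Mann-Whitney, where that value is only one rank. The +0.95-day shift therefore overstates what would reach the primary test.

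**Conclusion.** The point holds in this form: the stated endpoint, tests and analysis set leave a patient who dies on level 3 care either excluded, against intention-to-treat, or scored with a duration that death has cut short. Early deaths then look like fast recovery and late deaths like slow recovery, so the direction of bias cannot be known in advance.

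The size rests partly on the protocol and partly on assumption. From the protocol: at most 1.7 to 10.2 deaths in 34 patients, and a target of 0.585 days. Assumed: death times, mortality by arm, and normal durations with the mean and SD used for the sample size. On those, one day-1 death is worth 29% of the target effect, and mortality of 5% v 20% would give 11% to 19% false favouring of the worse arm. It would be tempting to say that the flaw will reverse the trial's conclusion. The documents do not support that: they give no mortality by arm and no death times. What they support is that a handful of deaths could move the primary result materially in a trial this small, and that the plan does not settle how.

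**What to change.** Before any comparison by arm, state one rule: death before final step-down from level 3 care is ranked worse than any observed duration. Make Mann-Whitney the primary test, without the preliminary normality test deciding between methods. Report deaths by arm and duration in survivors alongside. Treat the duration of inotropes and balloon support in the same way.

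One variable must be chosen. Days alive and free of level 3 care to day 30 is a related option but not the same: it treats deaths after step-down and intermittent care differently, and it can score a survivor still on level 3 at day 30 the same as a death.

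No new data are needed, since deaths to day 30 are already collected. The costs are these. The result combines death and duration and is no longer a difference in mean days. The stated 80% power at 34 rests on means without deaths and should be restated: in simulation about 66% at 5% and 55% at 10% equal mortality on level 3, so the sample size needs another look. Because the trial is single-blinded and the Trial status section reports 31 patients recruited, the change should be dated and documented as made without sight of outcomes by arm.

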### Pre-operation

Patients will be invited to participate in the trial if they are awaiting cardiac surgery. This includes elective patients and in-house referrals scheduled for revascularisation, valve surgery or both. Subjects with a recent history of an acute coronary syndrome or episode of decompensated heart failure (< 30 days) will be included. However, unstable subjects with medically refractory angina and/or pulmonary oedema requiring emergency surgery will be excluded from the trial.

After enrolment an ECG will be performed to confirm sinus rhythm and measure QRS duration and a transthoracic echocardiogram to measure ejection fraction using the Simpson's bi-plane method of discs. A detailed echo study will be performed (GE, Vivid 7, Horten, Norway), to evaluate LV systolic and diastolic function, valve function and cardiac dyssynchrony- Table 5. Subjects with EF > 35% will exit the trial.

**Table 5 T5:** Echo protocol.

Echo window	Modality	Measurement
Parasternal long axis	MMode	LV internal dimensions
		LV wall thickness
		Septum to lateral wall delay
	Colour flow	Mitral regurgitation

Parasternal short axis	PW doppler	RVOT- pulmonary pre-ejection interval (PPEI)
	CW doppler	PA acceleration time

Apical 4 chamber	2D	LA and RA area
		LVEDV and LVESV
	MMode	Long axis displacement- RV lateral/LV septal and
		lateral walls
	Colour flow	Mitral regurgitation
	PW doppler	Mitral inflow
		LVOT- aortic pre-ejection interval (APEI)
		IVRT
	MVI	Medial and lateral E'
		Basal segments- peak velocity.

Apical 2 chamber	2D	LVEDV and LVESV
	MVI	Basal segments- peak velocity.

Apical 3 chamber	MVI	Basal segments- peak velocity.

Echo measurements of dyssynchrony included:

• Interventricular mechanical delay (= APEI-PPEI)

• Atrio-ventricular delay (APEI)

• Time-delay to peak systolic velocity in the basal segments of the septal and lateral wall using myocardial velocity imaging (MVI) Q analysis.

A repeat transthoracic echo will be performed after discharge from the cardiac intensive care unit (CITU) between day 3 and 5 post surgery.

Baseline blood tests will be sent to measure:

• Full blood count (Haemoglobin, haematocrit and mean cell volume)

• Creatinine (eGFR calculation)

• TnT: Troponin T

• BNP: Brain naturetic peptide

• NGAL: Neutrophil gelatinase associated lipocalin- renal injury

Blood samples will be taken at baseline, 18 hours, 48 hours and 72 hours after admission to CITU.

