### Statistical Analysis

No previous studies have investigated the effect of BiV pacing on the duration of level 3 care after cardiac surgery; previous studies have reported the total duration of CITU stay.

Pokushalov et al [20] reported an average CITU stay of 3.9 ± 0.6 days in the subjects after cardiac surgery, compared with 2.5 ± 0.5 days in subjects who had BiV pacing after cardiac surgery - a 36% reduction. We anticipate that the duration of level 3 care will be shorter than the duration of CITU stay, perhaps with less variance, but we have used these mean values and standard deviations for our power calculation.

Using the standard formula described by Campbell and Matchin [23]:

$$\text{Sample}\;\text{size}=\frac{2\times {\left({\text{Z}}_{1\alpha }+{\text{Z}}_{2\beta }\right)}^{2}\times \sigma^{2}}{\delta^{2}}$$

σ = standard deviation of the population

δ = anticipated benefit from the intervention

(Z_1α _+ Z_2β_) = normal distribution of function

(1-β) = 80% and α = 5%.

From standard tables (Z_1α _+ Z_2β_) ^2 ^= 7.85

$$\text{Sample}\;\text{size}=\frac{2\times \left(7.85\right)\times 0.6^{2}}{{\left(0.15\times 3.9\right)}^{2}}=\frac{5.652}{0.342}=16.5$$

In order to demonstrate a 15% reduction in the duration of level 3 care, with power 80% and with p < 0.05 for a two-sided test, the estimated total sample size required is 34 subjects.

For haemodynamic comparison of paired data at 18 hours to compare BiV pacing to standard (AAI) pacing, Hanke et al [24] observed a cardiac index of 2.7 ± 0.6 L/min/ml^2 ^in the standard pacing group. Allowing a 0.3 L/min/ml^2 ^(11%) improvement in cardiac index with BiV pacing, significance 5% and power 80%, a sample size of 32 subjects would be required.

Considering both of these previous studies, the minimum number of subjects who will be recruited and randomised into this study, will be 34; allowing for a 1/3 drop-out rate, the minimum number to be recruited will be 45. In the 2 cardiac surgical centres in which this study will be performed the proportions of all patients undergoing cardiac surgery who have impaired LV function and sinus rhythm, and who would therefore be eligible for the study are 2% and 8% (approximately 65 patients in a total of 1414 operations per year); this study should therefore be feasible within a maximum of 2 years.

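### Biomarker change endpoints are adjusted for baseline only if the arms are seen to differ, with no criterion; always including the baseline value would be better and costs almost nothing

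*Protocol article*

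**What the plan says.** Four statements in the protocol article bear on this.

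- **Endpoint** (Endpoints): "Change in brain naturetic peptide, troponin T and neutrophil gelatinase associated lipocalin". The scale (absolute, log or percent) and the time point are not given.
- **Sampling** (Pre-operation): "Blood samples will be taken at baseline, 18 hours, 48 hours and 72 hours after admission to CITU". A baseline value of each biomarker is therefore planned for every patient.
- **Population** (Pre-operation): "Subjects with a recent history of an acute coronary syndrome or episode of decompensated heart failure (< 30 days) will be included". The minimisation factors in Table 6 are LV size, QRS duration, Euroscore, balloon pump, valve surgery and ejection fraction. Recent instability and baseline biomarker level are not among them.
- **Adjustment** (Statistical Analysis): "If continuous variables are not matched between intervention and control groups at baseline, inter-group comparisons will be made using an analysis of covariance". The model is to correct for whichever differences are found. This rule is not tied to any endpoint, so it is read here as covering the biomarkers. It gives no criterion for when groups count as unmatched.

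**The concern.** A change score subtracts the whole baseline value, which fixes the slope of post-operative on baseline level at 1. After bypass and cardioplegic arrest, much of the post-operative level, of troponin in particular, may reflect new operative injury, so the true slope may be well below 1. That is reasoning, not a figure in the article. If it is right, a patient who arrives with a raised value after a recent coronary syndrome shows a smaller rise for the same operative injury. An arm that by chance holds more such patients then looks better protected.

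The ANCOVA rule is meant to deal with this, but it acts only after an imbalance has been noticed and judged large enough. In a small trial a baseline difference can be big enough to matter and still pass as matched. When the rule is not triggered, the precision that the baseline value could give is lost. The abstract says that the effect of pacing on myocardial injury will be quantified, and this endpoint carries much of that aim.

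**Working it through.** **Size of the trial.** The article's own calculation reproduces: 2 × 7.85 × 0.6² / (0.15 × 3.9)² = 5.652 / 0.342 = 16.5, so 17 per arm and 34 in total. That figure is for the primary endpoint, and none is given for the biomarkers. I use 17 per arm and two-sided α = 0.05 below.

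**Assumptions not in the article.** The correlation ρ between baseline and post-operative level is shown at 0.2, 0.5 and 0.8. Data are normal on the analysis scale. Baseline and post-operative SDs are equal at first, and this is relaxed at the end. Unmatched is read as a baseline t test with p < 0.05, the only threshold the article states anywhere.

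**Precision.** With the post-operative variance set to 1, the change score has variance 2(1 − ρ) and ANCOVA has 1 − ρ². Their ratio is 2/(1 + ρ).

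| ρ | Change score | ANCOVA | Ratio |
|---|---|---|---|
| 0.2 | 1.60 | 0.96 | 1.67 |
| 0.5 | 1.00 | 0.75 | 1.33 |
| 0.8 | 0.40 | 0.36 | 1.11 |

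**When the rule triggers.** The standard error of a baseline difference is √(2/17) = 0.343 SD. Significance needs 2.037 × 0.343 = 0.70 SD. A difference of 0.5 SD gives t = 0.5/0.343 = 1.46 and p = 0.15, so it would pass as matched. By the normal approximation, a difference of at least 0.5 SD arises by chance in 14.5% of trials. About 5% of trials trigger the rule, which leaves about 9.5% with a difference above 0.5 SD and no adjustment. Simulation gives the same figure.

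**Conditional bias.** For a baseline difference b, the change-score comparison shifts by −(1 − ρ)b. At b = 0.5 SD the shift is 0.40 SD at ρ = 0.2, 0.25 SD at 0.5 and 0.10 SD at 0.8, in favour of the arm with the higher baseline. Among simulated trials with a difference near 0.5 SD, the false-positive rate under the conditional rule is roughly 8 to 9% at ρ = 0.2, 7 to 8% at 0.5 and 6% at 0.8.

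**Over all randomisations.** The change score has a mean difference of about zero under the null and a type I error of 4.9 to 5.0%. The conditional rule has 3.8 to 4.8%, so it is slightly conservative overall.

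**Power for a 1-SD effect (simulated).**

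| ρ | Change score | Conditional rule | Always adjusted |
|---|---|---|---|
| 0.2 | 61% | 62% | 81% |
| 0.5 | 81% | 81% | 89% |
| 0.8 | 99% | 99% | 100% |

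The conditional rule recovers almost none of the power that always adjusting gives.

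**Unequal SDs.** If the baseline SD is k times the post-operative SD, the change-score variance is 1 + k² − 2ρk. At k = 0.3 and ρ = 0.2 this is 1 + 0.09 − 0.12 = 0.97, against 0.96 for ANCOVA. The shift from a 0.5 SD baseline difference is (0.3 − 0.2) × 0.5 = 0.05 SD. Simulated power is about 82% for the change score and 81% always adjusted, so the gain is gone.

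**The case against.** The strongest reply is that the plan already contains the remedy. A reader might infer from the word change, and from "Normally distributed variables will be analysed using unpaired or paired Student's T tests respectively", that the biomarkers are tested with no adjustment at all. The article does not support that. The ANCOVA rule is general and these are continuous variables with a baseline sample. The t-test sentence follows "Data obtained for the primary endpoint and haemodynamic studies will be analysed for normality using the Kolmogorov-Smirnov test", which does not name the biomarkers.

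Two other strong readings also fail. The article does not say that the change is on the raw scale, and scale and time point can reasonably be left to a fuller document that is not shown. Nor is the comparison biased in the usual sense: randomisation makes a change score unbiased on average, and the bias exists only given an observed imbalance.

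The size is also open to challenge. It depends on ρ and on the ratio of the two SDs, neither of which the article gives. If operative injury makes post-operative values much more variable than baseline values, the gain can disappear, as the last calculation shows. Reading unmatched as p < 0.05 is likewise an assumption, and a stricter informal judgement would trigger adjustment more often.

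All of this stands and limits the point. It does not rescue the rule itself. Whether the main comparison is adjusted depends on a look at the data against a criterion that is not stated, although the baseline value is available for use in every case.

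**Conclusion.** The point holds in a limited form. For the BNP, troponin T and NGAL endpoints, an undefined, imbalance-triggered ANCOVA is a weaker choice than one that always includes the baseline value. With 17 per arm, equal SDs, normal data, a 1-SD effect and a p < 0.05 trigger, the cost is about 19 percentage points of power at ρ = 0.2 (81 − 62) and 8 at ρ = 0.5 (89 − 81). It is negligible at ρ = 0.8, and close to nil if the baseline SD is about 0.3 of the post-operative SD at ρ = 0.2. A chance imbalance of around 0.5 SD can go unadjusted and tilt the result towards the arm with the higher baseline. Overall type I error is not inflated. Severity is low: this is a secondary endpoint with no power claim attached, and the change is an improvement in method, not the repair of an invalid analysis.

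**What to change.** For these three biomarkers, replace the imbalance-triggered rule with a prespecified model. Compare the arms on the post-operative level at 18, 48 and 72 hours, by ANCOVA at each time or one repeated-measures model, with the patient's baseline value of the same biomarker always included as a covariate. If the values are skewed, preferably use the log scale for both baseline and outcome and report ratios of geometric means with 95% confidence intervals. Change from baseline can stay as a descriptive summary.

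The cost is about one sentence in the Statistical Analysis section. No new samples are needed, since the baseline blood tests are already scheduled. Two small consequences follow: on the log scale results are read as ratios instead of absolute changes, and a simple rule is needed for a patient with no baseline sample.
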